### **6.3.9 Post study adverse events and serious adverse events**

A post-study AE/SAE is defined as any event that occurs outside of the AE/SAE detection period defined earlier in this Section. Investigators are not obligated to actively seek AEs or SAEs in former study participants.

However, if the investigator learns of any SAE, including a death, at any time after a subject has been discharged from the study, and he/she considers the event reasonably related to the investigational product, the investigator will promptly notify the Study Contact for Reporting SAEs.

### **6.3.10 Treatment of adverse events**

Treatment of any adverse event is at the sole discretion of the clinical investigator and according to current good medical practice. Any medication administered for the treatment of an AE should be recorded in the subject's CRF.

The clinical research facility includes private consultation rooms, a procedure room, a resuscitation suite with oxygen, suction and resuscitation kits, and a post-vaccination observation room. An ambulance with suction and oxygen will be immediately available on vaccination days, and may be accessible with a short delay on the other days. The pharmacy at the MRU will have sufficient provisions to provide participants with oral and parenteral drugs for the treatment of common illnesses (including uncomplicated and severe malaria) free of charge, using essential medicines and treatment regimens that meet or exceed standards recommended by the Gabon Ministry of Health. Blood transfusion facility is available at all times. Twenty-four hour hospitalisation and basic emergency surgery services are available at the ASH adjacent to the MRU. Twenty-four hour nursing staffing and 24-hour on call physicians will be available.

If the investigators or the Local Safety Monitor judge that a participant requires hospitalization, this will be immediately facilitated and the investigators will ensure that the best possible treatment is offered.

## **6.4 Lost to Follow-up Procedures**

If a subject fails to appear for a follow-up examination, extensive effort (i.e., documented phone calls and certified mail) should be undertaken to locate or recall him/her or at least to determine his/her health status. These efforts should be documented in the subject's CRF and source documents.

[figure not shown]

## 7 EVALUATION CRITERIA

### 7.1 Primary Evaluation Criterion: Safety

#### 7.1.1 Definition of the Criterion

The safety profile will be assessed on the following criteria:

- Immediate reactogenicity (reactions within 30 minutes after each injection),
- Local and systemic reactogenicity measured from Day 0 to Day 14 after each dose
- Any unsolicited adverse event resulting in a visit to a physician between each injection and one month after the third dose.
- Any Serious Adverse Event (SAE) occurring from the inclusion through out the study. The relationship of the adverse event to the study vaccine will be established by the investigator, using the following definitions: related or not related.
- Biological safety, one month after each vaccination, in reference with the baseline before the first dose, by measuring the following:
  - RBC, haemoglobin, haematocrit, platelets, total WBC;
  - serum creatinine, ASAT, ALAT, total bilirubin, alkaline phosphatase.

#### 7.1.2 Parameters to be measured

The rate, duration and severity of signs and symptoms during the 14 days after the vaccination will be measured.

##### A. Local Solicited reactions

The following local reactions will be recorded and during the 14 days following the vaccination (D0 and D14 follow-up):

- **Pain:** Intensity and duration
- **Swelling:** Size (mm) and duration
- **Induration:** Size (mm) and duration
- **Erythema:** Size (mm) and duration
- **Pruritis:** presence or absence at injection site
- **Contra-lateral local reaction:** Intensity, duration and relationship with the vaccine

##### B. Systemic Solicited reactions

The following systemic reactions will be recorded during the 14 days following the vaccination (D0 and D14 follow-up):

- **Fever:** Intensity and duration and relationship with the vaccine
- **Irritability:** Intensity and duration and relationship to vaccine
- **Drowsiness:** Intensity, duration and relationship with the vaccine

[figure not shown]

- **Loss of appetite:** Intensity, duration and relationship with the vaccine
- **Diarrhoea :** Intensity, duration and relationship with the vaccine

### C. Unsolicited adverse events

For each unsolicited event/reaction the following details will be recorded:

1. Description of the event(s)/reaction(s),
2. Date and time of occurrence,
3. Duration,
4. Intensity,
5. Relationship with the vaccine,
6. Outcome.

## 7.1.3 Method and Timing of Measurement

### A. Local solicited reactions

The duration of the **pain** will be measured in days, and the severity scale as Grade 1 (mild): easily tolerated, does not interfere with daily life; Grade 2 (moderate): is discomfort that interferes with or limits usual daily activity; Grade 3 (severe): is disabling, inability to perform usual daily activity, including a functional limitation of the movement.

The duration of erythema, swelling, and other local reaction will also be measured in days. The size of erythema, and induration will be measured in mm with a rule. The maximum length will be reported on the CRF and given a code as shown below.

| Code | Size           |
|------|----------------|
| 1    | < 25 mm        |
| 2    | 25≤ and <50 mm |
| 3    | ≥ 50 mm        |

Solicited local reactions will be recorded at visits V2 to V17. The parents/guardians of the volunteers will report on scheduled visits the reactions they may experience, and the field workers will collect information and report on the field worker visit card as scheduled (See flow chart on page 9) after the vaccination.

### B. Systemic solicited reactions

The duration in hours or in days of all solicited systemic reaction will be monitored by the investigator, as well as the time interval of occurrence after the last vaccination.

Tympanic temperature will be measured with a digital thermometer and the intensity of fever will be defined as:

| Grade | Tympanic temperature |
|-------|----------------------|
| 1     | 38≤ and <38.5 °C     |
| 2     | 38.5≤ and <39 °C     |
| 3     | ≥ 39 °C              |

The solicited systemic reactions will be monitored at visits V2 to V17. The participants other daily the reactions will be detected on the field worker diary from during field worker visit days.

### C. Unsolicited adverse events

[figure not shown]

All unsolicited adverse events occurring between visits 2-17 shall be documented. If any of them fulfil the criteria of SAE described above in section 6.1.4, they will accordingly be documented and reported.

## 7.2 `Secondary Evaluation Criteria: Immunogenicity

### 7.2.1 Humoral Immune response

#### Definition

The humoral response to the vaccine antigens will be assessed by measuring the level of vaccine-specific IgG.

#### 7.2.1.1 Parameters to be measured

The level of GMZ2-specific IgG will be expressed as amount of IgG bound to the coated antigen. The comparator is a serial dilution of human IgG. A four parameter logistic-regression is fit to the IgG values and the OD-values expressed as amount of IgG bound. A pool of positive and negative control samples is always included in the measurements. Mean ratios with confidence intervals will be given. Four serial dilutions of sera will be done to enhance accuracy of the measurements.

#### 7.2.1.2 Method and Timing of Measurement

The vaccine-specific IgG will be assessed by ELISA for the recombinant proteins GMZ2 expressed in *L. lactis*; rGLURP and rMSP3 expressed in *E. coli*.

The measurements of vaccine-specific IgG responses will be performed at baseline, four weeks after each vaccination and one year after the first vaccination (at Day 0, 28, 56, 84 and 365). The final dataset will be generated after the last visit. Interim analyses will be performed if required and used for internal quality control of the final dataset.

### 7.2.2 Quality of the humoral Immune response:

#### Definition

The quality of the humoral immune response will be assessed by measuring, IgG1, IgG2, IgG3, IgG4 isotype responses to GMZ2 by ELISA (at Day 0 and 84).

#### 7.2.2.1 Parameters to be measured

The level of vaccine-specific IgG1, IgG2, IgG3 and IgG4 will be expressed as amount of bound Ig.

#### 7.2.2.2 Method and timing of measurement

The vaccine-specific IgG1, IgG2, IgG3 and IgG4 response will be assessed by ELISA for the recombinant proteins rGMZ2 expressed in *L. lactis*.

The measurements will be performed at baseline, and 4 weeks after the third vaccination (Day - 14 and 84). Experiments will be performed after Day 84.

### 7.2.3 Recognition of native antigens of *P. falciparum*

#### Definition

The quality of the antibodies elicited by the vaccine will be assessed by their ability to recognize the native antigen of air-dried *P. falciparum* mature schizonts.

[figure not shown]

### 7.2.3.1 Parameters to be measured

The titre of the antibodies will be expressed as the last serum dilution causing positive fluorescence as compared with non-specific background staining.

### 7.2.3.2 Method and timing of measurement

The plasma from subjects will be titrated by IFA (Immuno Fluorescence Assay) on slides containing *P. falciparum* mature schizonts using two parasite strains.

These measurements will be performed at baseline and four weeks after the second and the third vaccinations (days 0, 56, 84 and 365). All experiments will be performed after blinding in a different laboratory.

## 7.2.4 Antigen-specific memory B-cells

### Definition

Memory B-cell reactivity against GMZ2 will be measured by ELISPOT after stimulation of PBMC with IL-15 and CpG DNA for six days.

### 7.2.4.1 Parameters to be measured

Spots will be photographed and counted by microscopy by one investigator. Data will be presented as the frequency of antigen-specific B-cells (as percentage of the total IgG-positive memory B-cells per million PBMC).

### 7.2.4.2 Method and timing of measurement

B-cell ELISPOTs will be performed at Days 0, 84 and 365 on freshly isolated cells.

## 7.3 Exploratory Evaluation Criteria: Immunogenicity

### 7.3.1 Vaccine-specific Cellular Immune Response

#### 7.3.1.1 Functionality of the Immune response:

We propose to wait until the Growth Inhibition Assay in the presence of Monocytes (GIM) is validated. Meanwhile, a surrogate marker might be Western blotting. To do this, Vaccine antigens will be resolved using in SDS-PAGE and probed with 1:1000 dilutions of the sera. Bound antibodies are detected by HRP-labelled secondary antibodies and subsequent detection by chemiluminescence.

### Definition

The functionality of the antibodies will be assessed by measuring the ability of the antibodies to inhibit the growth *P. falciparum* parasites in the presence and absence of monocytes.

### 7.3.1.2 Parameters to be measured

The percentage growth inhibition will be determined as follows:

$$[(\% \text{ parasitaemia in control wells} - \% \text{ parasitaemia in test wells}) \times 100] / \% \text{ parasitaemia in control wells.}$$

The measurement will be done at baseline, after the second and the third dose of vaccination and one year after the first vaccination (at Days -14, 56, 84 and 365).

[figure not shown]

### 7.3.1.3 Method and Timing of measurement

An antibody and monocyte dependent growth inhibition assay will be performed as follows: parasites (F32) will be synchronized by sorbitol treatment and allowed to mature to trophozoite/schizont stages (PRBC). PRBC's will be adjusted to 4% haematocrit with culture medium (CM) and to 1% parasitaemia with O+ uninfected erythrocytes. Plasma samples from volunteers will be serially diluted in CM without Albumax II; 100 µl diluted plasma was added to the PRBC suspension in duplicate and incubated at 37°C for 42 hours in the presence or absence of monocytes.

Blood monocytes from healthy non-malaria exposed Swedish volunteers will be separated on Ficoll-Paque and re-suspended in 25% autologous serum. Adherent cells (97% viability) will be removed from a Petri dish after one hour incubation in autologous serum at 37°C in 5% CO2. Monocytes, 1.5x10^5 to 2x10^5/well, will be added to the PRBC/plasma suspension and incubated 42 hours at 37°C in 5% CO2. After incubation, cells will be harvested, washed and monolayers (30µl/well) will be prepared and fixed. Parasites will be stained with acridine orange (Fluka Chemie AG, Buchs, and Switzerland) and percentage of only newly infected erythrocytes (ring forms) will be determined per 40.000 erythrocytes in a fluorescence microscope. A serum pool from malaria immune Africans will be used as a positive control and a plasma pool from Swedish blood bank donors as negative control.

## 7.3.2 Evolution of Vaccine-specific Humoral Immune Response

### 7.3.2.1 Other antibody classes and modifications:

In addition to established IgG and IgG-subclass-analyses antibody class switching and age-related post-translational modifications are analysed.

#### Definition

The evolution of antibody classes and post-translational modifications will be assessed by measuring anti-GMZ2 IgM and modified anti-GMZ2 IgG on days -14, 84, and 365.

### 7.3.2.2 Parameters to be measured

The level of GMZ2-specific Ig classes and modifications will be expressed as amount of Ig bound to the coated antigen. The comparator is a serial dilution of human Ig. A four parameter logistic-regression is fit to the Ig values and the OD-values expressed as amount of Ig bound. A pool of positive and negative control samples is always included in the measurements. Post-translational modifications will be detected by specific antibodies, binding-substrates, and mass-spectrometry.

### 7.3.2.3 Method and Timing of Measurement

The measurements of vaccine-specific Ig responses will be performed at baseline, four weeks and one year after the first immunisation (at Day -14, 84 and 365). The final dataset will be generated after the last visit.

[figure not shown]

## 8 STATISTICAL METHODS AND DATA ANALYSIS

### 8.1 Principal Objective

To evaluate the safety of three doses of 30 µg and 100 µg GMZ2 adjuvanted with alum hydroxide and given at D0, D28 and D56, in healthy children aged 1-5 years old in Gabon.

### 8.2 Determination of the Sample Size

The total number of participants will be 30 divided into three groups of 10 each; one receiving 30 µg of GMZ 2, another 100 µg of GMZ2 and the other receiving rabies vaccine (control vaccine). The sample size chosen for this study are in line with similar safety and immunogenicity studies of similar candidate malaria vaccines published in the literature. As a phase I protocol, this study of 30 volunteers is not designed to detect adverse reactions that occur infrequently. Sample size was determined by the requirement to make a preliminary evaluation of inter-group and inter-individual variability, to avoid excessive risk and to allow realistic workload. Statistical significance may not be reached in such a study with low power; however, a non-significant finding would provide justification of the need for a study with greater power.

### 8.3 Data Set to be analysed

#### 8.3.1 Definition of Population

Given the above mentioned considerations it is planned to enrol 30 participants in the trial, to be randomised into the three treatment arms.

The statistical analysis shall be performed on two types of population depending on the participant's compliance to the protocol:

**i). Per Protocol:** the vaccination, blood sampling and visits number as well as the time-interval between vaccination and follow-up visits are respected, as they are defined in the protocol and in the flow chart. All participants who have not been compliant with the protocol will be excluded from this analysis but will be described in the final report. The protocol compliance criteria are the following:

- Participants fulfilling the inclusion and exclusion criteria
- Participants who have respected the number of vaccination and the time-intervals between the vaccination:
  - V2: 1st vaccination: D0, interval V1+2 weeks (± 3days)
  - V7: 2nd vaccination D28 , interval V2+4 weeks (± 3 days)
  - V12: 3rd vaccination D56 , interval V5+4 weeks (± 3days)
  - V17: Post vaccination D84 , interval V12+4 weeks (± 7days)
  - V18: Last study visit D365 , interval V17+ 9months (± 14days)
  - Subjects having respected the number of blood samples for biological safety evaluation, as well as the intervals between blood samples on Days -14, 28, 56, 84 and 365 within their applicable intervals

[figure not shown]

**ii). Intention to treat:** All participants who have received at least one vaccine dose will be included in the analysis. However, if a participant is not vaccinated for reasons unrelated to the primary outcome measure and the participants' code was broken during the period of the study that participant will be excluded from further analyses. In the event a participant withdraws from the study due to side effects, the last observation will be carried forward in all subsequent analyses (Last Observation Carried Forward LOCF) of the primary outcome measure.

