#### 3.1 Overview

- Randomized, controlled, double-blind phase I study
- One trial centre
- Safety oversight by a Safety Committee
- Study monitoring by AMANET
- Screening will be done within 14 days prior to the first vaccination
- Vaccination schedule will be on study days 0, 28 +/- 3, and 56 +/- 3
- Route of administration will be intramuscular on the deltoid muscle, alternately starting with the left side.
- Study duration will be approximately 13 months per participant
- Each participant will attend 16 standardised visits at the trial centre (Inclusion visit D-14; D0; D1; D3; D7; D14; D28; D29; D31; D35; D42; D56; D57, D70, D84, D365).
- Blood samples will be taken by venopuncture at five time points at D-14; D0; D28; D56; D84, and D365. Biological parameters and serological will be assessed at these time points as well as serological parameters. A maximum total of 7.5 mL blood will be taken at each blood sampling. For each participant a maximum of about 37.5 mL blood will be taken during the whole study.
- Twenty four hours, 3 days, 7 days and 14 days after each vaccination a visit is planned to monitor adverse events at D1, D3, D7, D14, D29, D31, D35, D42, D56, D57, D 59, D63 and D70
- Follow-up of serious adverse events (SAEs) until resolution
- The primary analysis will be conducted for all primary and secondary endpoints at a data-lock-point one month post vaccination 3 (study Day 84), after which the Primary

[figure not shown]

Study Report will be produced. These results will be used to decide on the go criteria for the next trial in children.

- The study will then continue in a single-blind fashion. Data gathered during this period will be reported in an addendum report.
- At the end of the study participants will be informed which vaccine they received and those who received malaria vaccine will be offered immunization with the rabies vaccine.

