### **3.5.3 Reasons for Withdrawal**

The following criteria will be checked at each visit. If any become applicable during the study, the participant will not be required to discontinue the study, but a separate immunogenicity analysis may be done that excludes these individuals.

- Use of any investigational drug or vaccine other than the study vaccine(s) during the study period.

[figure not shown]

- Chronic administration (defined as more than 14 days) of any dose level of immunosuppressants or other immune-modifying drugs during the study period and chronic daily use of inhaled steroids. Intermittent use of inhaled and topical steroids is allowed.
- Administration of a vaccine not foreseen by the study protocol during the period starting from 30 days before the first study vaccination and ending 30 days after the third vaccination.
- Administration of immunoglobulins and/or any blood products up to 30 days after the last study vaccination.

The following criteria will be checked prior to each vaccination and are contraindications to further vaccination. However, the study participants will be encouraged to continue to participate in the surveillance schedule for safety evaluation.

- Systemic hypersensitivity reaction following administration of the study vaccine. Severe (i.e., Grade 3) local reactions will be evaluated to determine whether or not further study vaccinations should be administered.

Participants may also withdraw voluntarily from receiving the study intervention upon request for any reason.

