### 4.3 Prior hand Concomitant Therapy

Immunosuppressive or immuno-modulator treatments are exclusionary criteria. If it happens to be necessary to use one of them during the trial period, the data of the concerned volunteers will be considered as deviation to the protocol. Antipyretics or analgesics will not be allowed as preventive treatment of pain or fever, before the vaccination.

Other vaccinations will not be allowed during a three month period before the first trial vaccine injection and within six months after the third trial vaccine injection. If a vaccination is necessary during the banning time window, the data of the subjects will be considered as deviation to the protocol.

For all other treatment, the following data will be specified and recorded on Case Report Forms:

- Trade name and generic name
- Total daily dose
- Start and stop dates (and, if appropriate, timing requirements within the day: AM, PM, post-shot)
- Indication

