**Day 7± 1 day: Post-vaccination 1 surveillance visit**  
**Visit 5**

- Verify and confirm ID of the participant
- Review history for any adverse events
- Targeted physical examination for solicited local and systemic symptoms
- Record tympanic temperature
- Record other signs/symptoms
- Give details of next visit and remind guardian on what to do if case of any problem

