**Day 84 ± 3 days: 4 weeks post-vaccination 3, surveillance visit**

**Visit 17**

- Countercheck to confirm the identity of the participant
- Record any complaints, symptom-directed physical examination, and examination of the injection site(s) for any abnormalities
- Record vital signs: tympanic temperature
- Assessment of the protocol local and systemic solicited events
- Collect 7.5 ml venous blood sample to measure:
  - FBC (EDTA) 2.5 ml.
  - Biochemistry, WB, ELISA, and GIM (Serum) 2.5 ml.
  - Peripheral blood mononuclear cells (PBMC) for memory B-cell ELISPOT 2.5 ml
- Provide further information on when the next visit should be
- Instruct the guardian to return to the MRU centre immediately should the participant manifest any signs or symptoms they perceive as important.

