## 8.4 Population used in analyses

The primary analysis will be conducted on all participants who have received at least one vaccine dose. Participants withdrawing for reasons related to the primary outcome measure, their last observation will be used in all subsequent analyses (LOCF).

Per protocol analysis of the secondary and exploratory outcome measures will be performed on all vaccinated subjects for whom serum samples are available.

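### The per-protocol set in 8.3.1 anchors dose 3 on the wrong visit, needs Day 365 data for an analysis locked at Day 84, and is contradicted by 8.4

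*Protocol*

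**What the plan says.** Protocol 8.3.1 restricts the per-protocol population to children who meet the entry criteria and keep to the number and timing of vaccinations, visits and safety blood samples, as set out in the protocol and the flow chart. Non-compliant children are excluded from that analysis. Its list includes:

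- first dose: "vaccination: D0, interval V1+2 weeks" (± 3 days);
- third dose: "V12: 3rd vaccination D56 , interval V5+4 weeks" (± 3 days);
- V17: Day 84, V12 + 4 weeks (± 7 days);
- V18: Day 365, V17 + 9 months (± 14 days);
- safety blood samples on Days -14, 28, 56, 84 and 365.

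Section 3.1 places the analysis of all primary and secondary endpoints at a data lock on Day 84, after which the study continues single-blind.

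Section 8.4 puts the primary analysis on all children with at least one dose. For the other outcomes it says: "Per protocol analysis of the secondary and exploratory outcome measures will be performed on all vaccinated subjects for whom serum samples are available".

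Other timing statements bear on the same criteria:

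- Section 3.1: "Screening will be done within 14 days prior to the first vaccination". Section 5.1 gives Days -14 to -1.
- Section 5.3, Visit 5: "Day 7± 1 day: Post-vaccination 1 surveillance visit".
- Section 5.3, Visit 17: "Day 84 ± 3 days: 4 weeks post-vaccination 3, surveillance visit".
- Section 4.3: "Other vaccinations will not be allowed during a three month period before the first trial vaccine injection and within six months" of the third dose. Section 3.5.3 instead uses a period "starting from 30 days before the first study vaccination and ending 30 days after the third vaccination".

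**The concern.** An analysis set must be determinable from data in hand when it is used, and must mean one thing. The 8.3.1 set fails on both counts. One of its criteria, read literally, cannot be met by any child vaccinated on schedule. Its full list cannot be evaluated at the only planned lock before the end of the study. Section 8.4 uses the same name for a different population.

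Per protocol is the only analysis that 8.4 names for the secondary and exploratory outcomes, which are the immunogenicity results. With 10 children per arm, moving one child in or out changes the denominator by 10% of an arm. Section 3.1 says the Day 84 results feed the decision on the next trial in children.

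**Working it through.** **Dose 3 anchor.** Inputs: V5 on Day 7 ± 1 and V12 on Day 56 ± 3 (5.3, flow chart); V7 on Day 28 ± 3.

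- The plan's Day 56 is reproduced from the flow chart's anchor: V7 + 4 weeks = 28 + 28 = Day 56.
- The anchor printed in 8.3.1 gives V5 + 4 weeks = 7 + 28 = Day 35.
- With windows: V5 on Days 6 to 8, plus 28, is Days 34 to 36; ± 3 gives Days 31 to 39. The schedule is Days 53 to 59. There is no overlap, and the nearest edges are 53 − 39 = 14 days apart.
- There are 3 × 7 × 7 = 147 in-window combinations of V5, V7 and V12 days. None meets the V5 criterion; 111 meet V7 + 28 ± 3. These are counts of day combinations, not forecasts of children. The other 36 fail because the ± 3 days is then counted from dose 2 and not from Day 0 (for example dose 2 on Day 25 and dose 3 on Day 59, 34 days apart).

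**Day 365 needed at Day 84.** 365 − 84 = 281 days. At the Day 84 lock no child has had V18 or the Day 365 sample, so nobody's membership under 8.3.1 can be settled. A child lost on, say, Day 200 would later drop out of the set and take valid Day 84 results along.

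**8.3.1 against 8.4.**

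| | 8.3.1 | 8.4 |
|---|---|---|
| Number and timing of doses | required | not mentioned |
| V17 and V18 windows | required | not mentioned |
| Safety blood samples | all five days | not mentioned |
| Serum available | not a listed criterion | required |
| Non-compliant child | excluded | included if vaccinated and serum exists |

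Both cannot be the per-protocol analysis.

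**Lesser conflicts.**

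- V18: nine months is taken as 274 days (assumption). With V17 on Day 84, 84 + 274 = 358, and ± 14 gives Days 344 to 372. The flow chart and Visit 18 give Day 365 ± 14 = Days 351 to 379. A visit on Days 373 to 379 is on schedule but fails 8.3.1. Taking nine months as 270 to 276 days moves the nominal day from 354 to 360.
- Screening: V1 + 14 ± 3 means V1 was 11 to 17 days before Day 0. Sections 3.1 and 5.1 allow 1 to 14 days. Only Days -14 to -11 satisfy both, 4 of 14 permitted days.
- V17: ± 7 days (Days 77 to 91) in 8.3.1 and the flow chart, but ± 3 days (Days 81 to 87) in 5.3.
- Other vaccinations: three months before to six months after in 4.3, against 30 days before to 30 days after in 3.5.3.

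**The case against.** The best reply is that nobody would be misled. The V12 line itself carries D56, 8.3.1 refers to the flow chart, and the flow chart and 5.3 agree on Day 56 ± 3. That stands: V5 has one sensible correction, and a reader who infers that the per-protocol set will in practice be empty goes too far.

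Nor do the intervals in 8.3.1 contradict the schedule generally. V2, V7 and V17 match the flow chart; only V12 and V18 do not. The V2 and V17 conflicts are with the text of sections 3 and 5. The count of 4 in 14 screening days is of calendar days, not children, and 5.1 lets Visit 1 spread over more than one visit, so the date that anchors V1 is itself open.

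It is also fair that the harms do not all arise together. If 8.4 governs, visit windows exclude nobody and a child lost after Day 84 keeps the Day 84 result. The exclusions follow only if 8.3.1 governs. The fault is that the protocol does not say which does.

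A reader might infer that the choice of set will be made after unblinding. No section says so. Section 8.7.1 requires the analysis plan to be agreed before the lock for the final analysis, which leaves the position at the Day 84 analysis unstated; it does not show a late choice.

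Finally, 8.6 makes the analysis descriptive and 8.6.2 rules out hypothesis tests on secondary outcomes. This limits the consequence but does not make the set determinable.

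**Conclusion.** The point holds for three faults: the V5 anchor, the Day 365 requirement for a Day 84 analysis, and the second meaning of per protocol in 8.4. The first is clerical, with windows of Days 31 to 39 against Days 53 to 59. The other two would remain after the slip was corrected. The V18, screening, V17 and other-vaccination conflicts are smaller; the V18 one amounts to about a week and rests on V17 falling on Day 84 and on nine months being 274 days. The other-vaccination windows are not in the 8.3.1 list and do not by themselves undermine it.

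The damage is confined to the secondary and exploratory outcomes. The primary safety analysis uses all children with at least one dose and is untouched. This should be fixed before the Day 84 lock, but it does not threaten the primary result.

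**What to change.** - In 8.3.1, correct the V12 anchor so that it agrees with D56 on the same line and with the flow chart, and say whether the ± 3 days is counted from Day 0 or from the previous dose.
- Define per-protocol sets by time point. The Day 84 set needs compliance only through V17; the Day 365 set adds V18 and the Day 365 blood sample.
- Do not exclude a child from per protocol for a screening date that 3.1 and 5.1 allow.
- In 8.4, give the set of all vaccinated children with a sample its own name, and state before the Day 84 lock which set is used for the immunogenicity analyses.
- Have the sponsor reconcile the V17 window (8.3.1 and flow chart against 5.3), the V18 anchor (8.3.1 against flow chart) and the other-vaccination windows (4.3 against 3.5.3).

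The cost is wording in the protocol and the analysis plan. The analysis-set changes need no new visits, samples or participants.
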